### Endpoints

The primary endpoint is non-response to CRT defined as the combination of all-cause mortality, hospitalization for heart failure, and unchanged or worsened functional status. The primary endpoint is attained if the patient is registered for one of the following three events during follow-up: (1) death from any cause, (2) hospitalization for heart failure, or (3) no improvement in NYHA class *and* <10% improvement in 6MWT.

Hospitalization for heart failure is defined as admission to the hospital lasting more than 24 hours with symptoms of congestive heart failure and subsequent intravenous treatment for heart failure.

Secondary endpoints include all-cause mortality, hospitalization for heart failure and changes of the following variables during follow-up: NYHA class, 6MWT, quality of life, Nt-ProBNP, LV EF, LV EDV and ESV, LV dyssynchrony and mitral regurgitation grade. Also, procedure time for CRT implantation, ability to place the LV lead in the first or second prioritized CS branch, complications and final lead positions are recorded.

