### Sample size

The study is designed to detect a clinically meaningful difference between standard and imaging guided LV lead positioning in CRT as measured by applying a clinical composite endpoint. The underlying assumptions for the primary endpoint are based on data from previous trials in comparable patient cohorts demonstrating a 50 to 70% response rate to CRT [1,2,4,30]. Accordingly, we expect a 60% response rate in the group with empiric LV lead placement and hypothesize an 80% response rate in the group with imaging guided LV lead positioning. Thus, we estimate a 20% difference in the percentage of patients reaching the primary endpoint. To identify this increase in response rate and to achieve a statistical power of 80% a sample size of 182 patients is needed (given a two-sided alpha value of 0.05). The sample size calculation does not account for the stratified randomization [31]. To compensate for an expected loss of follow-up in approximately 5% of the patients, a total of 192 patients are included. Sample size calculation was performed using commercially available statistical software (Stata version 12, StataCorp, College Station, TX, USA) to estimate the sample size for a two-sample comparison of proportions.

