### Statistical analysis

Demographic and baseline characteristics of both intervention groups are presented and compared clinically. At follow-up, a Pearson’s *χ*^2^ or Fisher’s exact test when appropriate is used to compare categorical variables. Normally distributed continuous variables are compared using Student’s *t*-test. Continuous variables not normally distributed are compared using a Wilcoxon’s rank-sum test. Forty patients will be randomly selected for assessing intra- and interobserver variability for the dyssynchrony measurements using linear regression and Bland-Altman analysis. In the same 40 patients, kappa statistics are computed to assess intra- and interobserver agreement of site with latest mechanical activation and final LV lead position. All analyses will be conducted according to the intention-to-treat principle. Multiple imputation will be applied in case of missing data [32]. A two-sided *P-*value of <0.05 is considered to be statistically significant. Statistical software (Stata version 12, StataCorp, College Station, TX, USA) is used for statistical analysis.

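### Multiple imputation is paired with tests that do not all pool, and the primary comparison has no effect estimate and ignores the coronary artery disease stratum

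*Protocol article*

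**What the plan says.** All points are from the protocol article.

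- **Categorical variables (Statistical analysis).** Pearson's chi-square or Fisher's "exact test when appropriate is used to compare categorical variables". The primary endpoint, response or non-response, is binary and falls under this sentence.
- **Continuous variables (same section).** "Normally distributed continuous variables are compared using Student"'s t-test; "Continuous variables not normally distributed are compared using a Wilcoxon" rank-sum test.
- **Missing data and population (same section).** "Multiple imputation will be applied in case of missing data", and "All analyses will be conducted according to the intention-to-treat principle". Significance is a two-sided P-value below 0.05.
- **Primary endpoint (Endpoints).** "The primary endpoint is attained if the patient is registered for one of the following three events during follow-up": death, heart-failure hospitalization, or functional non-improvement. The last needs both no gain in NYHA class and "<10% improvement in 6MWT".
- **Randomization.** Stratified by presence or absence of coronary artery disease. Allocation data are released once every patient has finished follow-up.
- **Sample size.** 182 patients, raised to 192 for about 5% loss. The section says that the calculation makes no allowance for the stratification.

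**The concern.** Multiple imputation produces several completed data sets. Its result is a combination of one estimate and one standard error per data set. A method that returns only a P-value, as Fisher's exact test and the Wilcoxon test do, gives Rubin's rules nothing to combine. Pearson's chi-square returns a statistic, which can be combined only under a further rule. The article states both halves, the tests and the imputation, but names no quantity that links them. Read literally, the 0.05 threshold has several P-values to be set against.

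The named tests are also unadjusted, although randomization is stratified on coronary artery disease. A model that carries the stratum would resolve both points at once: it yields an estimate that pools, and it matches the analysis to the design.

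At stake is whether the trial has one primary result fixed in advance. Neither the sample size nor the choice of endpoint is in question.

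**Working it through.** **1. The plan's own figure.** Inputs from Sample size: "we expect a 60% response rate in the group with empiric LV lead placement", 80% in the imaging arm, two-sided alpha 0.05, power 80%, 1:1 allocation.

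- Without continuity correction: n = [1.96·√(2·0.7·0.3) + 0.842·√(0.6·0.4 + 0.8·0.2)]² / 0.20² = (1.270 + 0.532)² / 0.04 ≈ 81.2, so 82 per arm, 164 in total.
- With continuity correction: n' = (81.2/4)·[1 + √(1 + 4/(81.2·0.20))]² ≈ 90.9, so 91 per arm, **182** in total.
- Loss: 182/0.95 = 191.6, so **192**. Expected missing: 192 × 0.05 = 9.6, about 10 patients.

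Both stated figures reproduce and are not disputed.

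**2. Which named tests pool.** For M data sets with estimates Q and variances U, Rubin's rules need the mean of Q and T = W + (1 + 1/M)·B, where W is the mean of U and B the variance of Q.

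| Test | Gives Q and U? | Route to one result |
|---|---|---|
| Student's t | Yes, mean difference and SE | Rubin, direct |
| Pearson chi-square | Statistic only | D2 rule, or replace by the risk difference from the same 2×2 table |
| Fisher exact | No | No standard Rubin pooling |
| Wilcoxon rank-sum | No | No standard Rubin pooling |

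**3. Which test the primary endpoint would use.** At the planned rates with 96 per arm, non-responders total 96 × (0.40 + 0.20) = 57.6, so the expected count per arm is 28.8. That is well above the usual small-count trigger (expected count below 5) for Fisher. The primary test would be Pearson.

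**4. Does the combining step matter?** Simulation: 4,000 trials, 96 per arm, outcomes missing completely at random, 20 imputations within arm. The pooled risk difference here is unadjusted. With X² the Pearson statistic in each data set and r = (1 + 1/M)·Var(√X²), D2 = [mean X² − r·(M+1)/(M−1)] / (1 + r).

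| Missing | Response rates | Rubin risk difference | D2 Pearson | Complete cases | Data sets disagree on P<0.05 |
|---|---|---|---|---|---|
| 5% | 60% vs 80% (power) | 0.85 | 0.84 | 0.85 | 19% |
| 5% | 70% vs 70% (type I error) | 0.056 | 0.052 | 0.051 | 11% |
| 10% | 60% vs 80% (power) | 0.84 | 0.83 | 0.84 | 26% |
| 10% | 70% vs 70% (type I error) | 0.056 | 0.052 | 0.052 | 18% |

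The 5% rows are the plan's expectation; 10% is an assumed worse case. Monte Carlo error on a type I error of 0.05 is √(0.05·0.95/4000) ≈ 0.003, so the three routes are close.

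**5. Choice between the categorical tests.** Take 91 observed per arm at the planned rates (55 and 73 responders) and 5 missing per arm. If all missing empiric-arm patients respond and all missing imaging-arm patients do not, the table is 60/96 vs 73/96: Pearson P = 0.042, Fisher P = 0.060. In the opposite extreme, 55/96 vs 78/96, Pearson P = 0.0003. These are limits, not expected results.

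**6. What the composite rule already settles.** Under Endpoints, a recorded death or heart-failure hospitalization makes the patient a non-responder whatever else is missing. With neither event, an observed gain in NYHA class, or a walk-test gain of at least 10%, rules out the functional component. Only patients outside these cases have an undetermined outcome.

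**The case against.** The strongest reply has three parts.

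- **The primary test can be pooled.** Pearson would apply at the planned rates, and pooling by D2 held its level (0.052) with power 0.84, about the same as the pooled risk difference. This stands. A reader might infer that the primary test can give no single answer; that goes too far. What remains is that neither D2 nor an effect estimate is named, and that Wilcoxon has no such route for the non-normal secondary variables.
- **An article condenses.** The imputation model, number of imputations and sensitivity analyses may sit in a fuller document. This stands too, and their absence is not charged here. The point concerns what the article does state: tests that do not all fit the stated missing-data method and that leave out the stratification factor.
- **Known outcomes are not at risk.** A reader might infer that imputation would overwrite outcomes already settled by death, hospitalization or observed improvement. The documents do not support this: imputation is confined to missing data, the endpoint rule fixes those outcomes, and nothing says that the composite is imputed as a single variable.

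A reader might also size the problem by moving five patients in one arm, 5/96 = 5.2 points. That assumes every missing patient in that arm switches the same way, which pooled imputation does not do, so it does not measure this defect. Nor does the article say that analysis choices stay open until allocation is released, or that complete cases are the fallback.

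**Conclusion.** The point holds in a limited form. The stated tests and the stated imputation do not all fit together: Fisher and Wilcoxon cannot be pooled by Rubin's rules, Pearson needs an unnamed rule, the primary endpoint has no effect estimate, and the comparison disregards the stratum.

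Because imputed data sets disagreed on significance in about 11% to 19% of simulated trials at 5% loss, the combining step cannot be left implicit. Once it is fixed, power and type I error hardly depend on the route. The gain is therefore a single primary result, set in advance and consistent with the stratified design, and not extra power.

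This rests on about 5% loss, outcomes missing completely at random, and the planned response rates. The effect of adding the stratum was not quantified, since the documents give no response rates by coronary artery disease. The importance is moderate to low.

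**What to change.** Before randomization data are available:

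1. Make the primary analysis a risk difference with 95% CI from a binomial model with treatment and coronary artery disease stratum, estimated in each imputed data set and pooled by Rubin's rules. An odds ratio from a logistic model with the same terms is an acceptable alternative. Name one. The risk difference matches the scale of the 20-point sample-size assumption.
2. For non-normal secondary endpoints with imputed data, replace the Wilcoxon test with a model-based estimate that pools, such as a mean difference on a transformed scale.
3. As a clarification only, add one sentence: undetermined NYHA or walk-test components are imputed, the composite is then derived, and outcomes already determined under Endpoints stay as recorded.

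The cost is revised analysis wording and a little programming. No new data are needed, and the sample size stays at 182/192.

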## Discussion

The introduction of CRT has improved the treatment of heart failure patients [1-4]. However, 30 to 50% of patients continue to remain non-responsive to this pacing strategy [1,2,4]. Optimal placement of the LV pacing lead has been shown to be a crucial determinant of CRT response [6-8]. The ImagingCRT study is a randomized trial designed to test the hypothesis that multimodality imaging guided LV lead positioning can increase the response rate to CRT as compared with standard LV lead placement.

Several retrospective echocardiographic studies using speckle tracking demonstrated greater reverse LV remodeling and superior long-term prognosis in patients with LV pacing concordant to the site of latest mechanical activation when compared to patients with discordance between LV lead position and the area with latest activation [7,10,26]. Accordingly, in this study, assessment of the latest mechanically activated LV segment is performed using speckle tracking 2D radial strain.

Recent studies used speckle tracking low-amplitude LV radial strain as a surrogate measure of myocardial scar to demonstrate a poor CRT response when the LV lead was placed in regions with low-amplitude radial strain [7,33]. A 2012 assessor-blinded, prospective randomized study found increased response rate to CRT using speckle tracking radial strain to assess the site of latest activation and as a measure of scar to guide LV lead placement as compared to standard therapy [16]. However, low-amplitude radial strain may also occur in non-ischemic heart failure patients with dilated LVs without myocardial scar [34]. Retrospective magnetic resonance imaging (MRI) and SPECT studies have demonstrated an unfavorable outcome after CRT when the LV lead is positioned in areas with transmural myocardial scar [6,9,12]. Myocardial scar quantification by SPECT is well validated in the literature and a practical approach for current clinical practice [14]. Consequently, SPECT imaging is performed for localization of myocardial scar in the current study. The LV 17-segment model is used for optimal agreement with echocardiography and cardiac CT [29].

Visualization of cardiac venous anatomy by cardiac CT is feasible and comparable to venography [15]. Cardiac CT can reveal the presence of specific CS tributaries and provide information on vessel course, side branches and diameters prior to CRT implantation. Thus, cardiac CT may further facilitate LV lead positioning to the optimal pacing site. Therefore, in this study, a cardiac CT is performed prior to CRT implantation.

Prior studies evaluating the effect of LV lead position on outcome after CRT have used post-implantation chest radiography, some combined with fluoroscopy, to determine final LV lead position [7,9,10,16,33]. However, chest radiography and fluoroscopy are poor predictors of LV lead position compared to cardiac CT [35,36]. Accordingly, we apply cardiac CT for assessment of LV lead position.

The criteria for response to CRT used in both prospective and retrospective studies investigating the effect of LV lead placement have been variable and often limited to changes in LV systolic dimension [7,10,16]. In contrast, we apply a robust composite endpoint combining subjective and objective derived measurements representing a global assessment of the patient [37].

### Limitations

We acknowledge the inherent limitations of the single-center study design. Nevertheless, this is a relatively large prospective, patient- and assessor-blinded, randomized study evaluating the effect of multimodality imaging guided LV lead placement on the response rate to CRT.

We do not merge the different imaging modalities. However, visualization of CS tributaries by cardiac CT can easily be related to the clockwise method for fluoroscopic CS visualization, which, again, may be correlated to the LV segmentation used for myocardial SPECT and echocardiography, respectively. Another limitation is the lower spatial resolution of scar quantification by SPECT as compared to MRI. However, a substantial minority of our patients is not eligible for MRI because of an indwelling device.

Because of the radiation exposure associated with, for example, cardiac CT and SPECT, there has been much scrutiny on the increasing use of diagnostic cardiac imaging [38]. Several approaches to minimize radiation dose are applied in this study, including the use of iterative reconstruction algorithms, application of prospectively triggered high pitch CT scan, individual settings of tube voltage and current, tube current modulation with narrow full current window, and the use of ^99m^Tc-agents in SPECT, respectively [39]. However, the introduction of cardiac CT and SPECT into the diagnostic algorithm prior to CRT will increase the cumulative radiation exposure of patients. In the age group investigated in this study, however, the stochastic risk of radiation-induced cancer may likely be outweighed by the potential benefit of multimodality imaging guided LV lead placement in CRT.

### Perspective

Despite tremendous advances in knowledge and experience with CRT, the proportion of patients considered clinical non-responders have remained stable since the introduction of CRT. The effect of imaging guided LV lead placement on CRT response rate, as tested in this study, can make an important contribution in the pursuit of increasing response rate to CRT.

### Trial status

The trial is ongoing. The first patient was randomized on 11 April 2011. As of August 2012, 88 subjects had been included. Enrollment completion is expected by September 2013.

## Abbreviations

2D: Two-dimensional; 3D: Three-dimensional; 6MWT: Six-minute-walk test; AV: Atrioventricular; CRT: Cardiac resynchronization therapy; CRT-D: CRT-implantable cardioverter defibrillator; CRT-P: CRT pacemaker; CS: Coronary sinus; CT: Computed tomography; eCRF: Web based case record form; EDV: End-diastolic volume; EF: Ejection fraction; ESV: End-systolic volume; LAO: Left anterior oblique; LBBB: Left bundle branch block; LV: Left ventricle/ventricular; MRI: Magnetic resonance imaging; NT-ProBNP: N-terminal pro b-type natriuretic peptide; NYHA: New York Heart Association; RAO: Right anterior oblique; RV: Right ventricle/ventricular; SPECT: Single-photon emission computed tomography; TDI: Tissue Doppler imaging; VV: Interventricular.
